### Monitoring, Quality Control, and Data Management

An auditor who is independent from the departments involved in the trial, including those responsible for monitoring, will inspect the medical institution and other facilities involved to ensure that the trial is conducted appropriately.

### Ethical Considerations

This trial will be conducted in compliance with the Declaration of Helsinki, Pharmaceutical and Medical Device Act, Ministerial Ordinance on Good Clinical Practice for Medical Devices, and all other guidelines in relation to these regulations (jRCT2032220603). This study was approved by the institutional review board of the University of Tokyo School of Medicine (approval number 2022012-11DY). We will obtain written informed consent from all study participants. All patient data will be anonymized. Patients will be compensated JPY 7000 (approximately US $50) for each visit to the hospital.

### Outcome Measures

#### Primary Outcome

The primary outcome of this study is the between-group differences in the change of HbA_1c_ value between baseline (V2) and either the end of the intervention period (week 24 [V8]) or, for patients who discontinue before V8, the point of discontinuation. Reduction of HbA_1c_ level by 0.35 percentage points is considered to be clinically significant [54,55].

#### Secondary Outcomes

Secondary outcomes (Table 3) include health measures, measurements of steps, measurements of other behavior changes, and assessments of app use. We will also assess safety outcomes such as hypertension requiring medical assistance (assessed from the system records), subjective hypoglycemia, pain in the lower back and lower extremities (tarsus, thighs, knees, calves, shins, ankles, and feet), and any other adverse events (all assessed through patient interviews).

**Table 3 table3:** Secondary outcomes investigated in the study—22 areas spanning health outcomes, exercise outcomes, other behavior changes, and app assessments.

Categories and item numbers		Outcomes
**Health outcomes**		
	1	HbA_1c_^a^ level (%) Change in HbA_1c_ level^b^ Proportion of patients with HbA_1c_ level <7%^c^
	2^d^	FBG^e^ (mg/dL) >5 hours after a meal
	3^d^	eGFR^f^ (L/min/1.73m2)
	4^d^	BMI (kg/m2)
	5^g^	Body weight measured at home (kg)
	6	Systolic and diastolic BP^h^ (mm Hg) BP measured at hospital^d^ BP measured at home^g^
	7^d^	HDL^i^ (mg/dL), LDL^j^ (mg/dL), and TG^k^ (mg/dL)
	8^l^	Concomitant medication intake (type of medication and daily dosage or weekly dosage for weekly formulation) Change in type 2 diabetes medication intake (either increased, unchanged, or reduced) Introduction of new medications to treat type 2 diabetes, hypertension, or dyslipidemia
	9^d^	Type 2 diabetes–related emotional distress (assessed using Problem Areas in Diabetes) [45]
	10^d^	Type 2 diabetes–dependent quality of life (assessed using Audit of Diabetes-Dependent Quality of Life) [53]
**Exercise outcomes**		
	11^g^	Daily step count
	12^d^	Walking duration
**Other behavior changes**		
	13^d^	Locomotive syndrome (assessed using Locomo 25) [46]
	14^d^	Type 2 diabetes self-care, assessed using the Japanese version of the Summary of Diabetes Self-Care Activities Measure [51]
	15^d^	Self-management behaviors related to physical activity, assessed using Evaluation Scale for Self-Management Behavior Related to Physical Activity of Type 2 Diabetic Patients [47]
	16^d^	Self-regulation of physical activity, assessed using the Japanese version of Physical Activity Self-Regulation Scale–12 [50]
	17^d^	Changes in walking self-efficacy: Self-efficacy for achieving the targeted daily steps [48] Self-efficacy for dealing with barriers to achieving the targeted daily steps (assessed using Self-Efficacy Scale of Walking Behavior) [49]
	18^d^	Changes in self-efficacy in health-promoting behavior, assessed using Positive Coping Behavior Towards Illness subscale within Self-Efficacy Scale for Health Promoting Behaviors [52]
	19^m^	Health literacy, assessed using Health Literacy Scale 14 [56]
**App assessments**		
	20^n^	App use is assessed through the following: Recording rate of body weight, step count, and BP and its change^o^ Goal achievement rate^p^ Goal increment rate^q^ Goal reduction rate^r^ Average number of coping planning strategies implemented per day^s^ Number of barrier identifications^t^
	21^u^	System feasibility and usability (only for the intervention group)
	22^v^	Number of emails, SMSs, and calls to encourage registration

^a^HbA_1c_: hemoglobin A_1c_.

^b^Includes both differences between week 0 (registration at V2) and week 12 (V5; or point of discontinuation, if earlier) and between week 0 (registration at V2) and week 36 (V9; or point of discontinuation, if earlier), which are compared within group and between groups, and includes the difference between week 0 (registration at V2) and week 24 (V8; or point of discontinuation, if earlier), which are compared within group.

^c^Includes all 3 proportions that are compared between groups: latest HbA_1c_ level up to week 12 (V5; or point of discontinuation, if earlier) <7%, latest HbA_1c_ level up to week 24 (V8; or point of discontinuation, if earlier) <7%, and latest HbA_1c_ level up to week 36 (V9; or point of discontinuation, if earlier) <7%.

^d^Includes all 3 differences: between provisional registration (V0) and week 24 (V8; or point of discontinuation, if earlier), between provisional registration (V0) and week 12 (V5; or point of discontinuation, if earlier), and between provisional registration (V0) and week 36 (V9; or point of discontinuation, if earlier), which are compared between groups.

^e^FBG: fasting blood glucose.

^f^eGFR: estimated glomerular filtration rate.

^g^Includes differences between the beginning of the intervention (V2; or from baseline period [V1] for steps) and week 4 (V3) and differences between each visit and each subsequent visit, which are compared between groups. In addition, they include measurements at each period (between visits), which are to be compared between groups. Item 11 also includes difference between baseline (V1) and 2 weeks before week 12 (V5; or point of discontinuation, if earlier) and week 24 (V8; or point of discontinuation, if earlier), which are compared within group and between groups.

^h^BP: blood pressure.

^i^HDL: high-density lipoprotein.

^j^LDL: low-density lipoprotein.

^k^TG: triglyceride.

^l^Includes assessment at week 12 (V5), week 24 (V8), and week 36 (V9; or point of discontinuation, if earlier), respectively, and it will be compared between groups.

^m^Will be assessed at provisional registration (V0).

^n^Includes comparisons of the differences over the first period of the intervention (from week 0 [V2] to week 4 [V3]) and differences over each subsequent period (between subsequent visits), which are compared between groups (only the recording rate of body weight, step count, and BP and its change) and within group (all assessments).

^o^Formula: (number of days in which measurements for BW, step count, and BP are recorded/total number of days) × 100.

^p^Formula: (number of days in which step goal was achieved/total number of days) × 100; examined only for the intervention group.

^q^Formula: (number of days in which step goal was increased/total number of reset times) × 100; examined only for the intervention group.

^r^Formula: (number of days in which step goal was reduced/total number of reset times) × 100; examined only for the intervention group.

^s^Formula: total number of coping strategies implemented over the period/total number of days; examined only for the intervention group.

^t^Number of barriers identified every 4 weeks; examined only for the intervention group.

^u^Will be assessed for the intervention group only, at week 24 (V8; or point of discontinuation, if earlier).

^v^Will be assessed at week 24 (V8; or point of discontinuation, if earlier).

### Statistical Analysis

In this study, we define 3 analysis populations: full analysis set (FAS), per protocol set (PPS), and safety analysis set (SAS). FAS is the set of all patients whose data were obtained at least once after randomization. We will follow the intention-to-treat principle and analyze data based on the assigned group in the FAS analysis. PPS is the FAS population with the exclusion of patients who were found to have violated the eligibility criteria after randomization or who did not use the app over a 3-week period. SAS is the set of all patients who used the StepAdd app or the placebo app at least once after randomization. In the safety analysis using SAS, we will analyze data based on the apps actually used by the patients, regardless of allocation. AS will be the primary analysis population, and PPS will provide supportive results. All safety analyses will be conducted in SAS.

Data about patients’ characteristics will be presented as mean, SD, minimum, 25th percentile, median, 75th percentile, and maximum for continuous variables and as frequency and proportion for categorical variables.

In the primary analysis, we will perform between-group comparison of the change in HbA_1c_ level from week 0 (V2) to week 24 (V8; or point of discontinuation, if earlier) using analysis of covariance, including baseline HbA_1c_ level (ie, HbA_1c_ level at week 0 [V2]) as a covariate in FAS. If participants discontinue the study, the latest measurement of HbA_1c_ level before V8 will be used.

We will also conduct 2 subgroup analyses with one classification by HbA_1c_ level at week 0 (V2; either <8.5% or ≥8.5%) and the other classification by BMI at the time of initial registration (V0; either <25 kg/m^2^ or ≥25 kg/m^2^). We will conduct subgroup analysis on the primary outcome in each analysis set to investigate whether the efficacy of StepAdd is consistent between these subgroups.

We will conduct statistical analysis of safety outcomes. We will compare the proportion of incidences of hypoglycemia, joint pain, significantly elevated BP (≥145/95 mm Hg), and exacerbations of joint pain between groups using Fisher exact test. Other adverse events will be recorded using the Japanese version of the Medical Dictionary for Regulatory Activities categories for Preferred Term and System Organ Class, and their incidence proportions will be compared between groups using Fisher exact test. The severity of each incidence will be categorized into 3 grades (low, moderate, and high), and their between-group comparison will be conducted using the Cochran-Mantel-Haenszel test.

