### Patient Recruitment

Patients will be recruited at 5 medical institutions in Japan: University of Tokyo Hospital, Akita University Hospital, Yokohama City University Hospital, Yokohama City University Medical Center, and Yokohama Rosai Hospital. Recruitment will be conducted by attending physicians during patients’ regular consultations at outpatient clinics. Recruitment will be conducted over 2 years, starting from January 1, 2023, and ending on December 31, 2024.

To detect 0.35% difference in the primary outcome (change in HbA_1c_ level), assuming an SD of 0.74% as seen in a previous study [40], and to achieve a 2-sided significance level of .05 and a statistical power of 80%, the minimum sample size is 72 patients per group [41]. On the basis of an assumed dropout rate of 10%, we are targeting to recruit a total sample of 160 patients (n=80, 50% in the intervention group; n=80, 50% in the control group).

All participants will receive a thorough written and verbal explanation about participation. We will subsequently obtain written informed consent from all study participants before screening for eligibility to participate in the study. If findings regarding efficacy and safety that may affect patient consent are discovered at any points during the trial, we will swiftly disclose this information to participants and acquire their renewed consent.

To focus on patients who are likely to benefit and likely to be capable of participating, we will recruit patients who meet all the inclusion criteria (Textbox 2). To ensure that patients can safely and effectively participate in the intervention, we will recruit patients who do not meet any of the exclusion criteria (Textbox 3). We will use a transtheoretical model (TTM) questionnaire to categorize the participants who are currently at the contemplation stage (willing to change health behavior within the next 6 months), preparation stage (willing to change health behavior within the next month), or action stage (has made modifications to health behavior) [42]. In our previous study, patients who were in the contemplation and preparation stages of TTM were more likely to prefer to use smartphone-based self-management tools than those in the precontemplative stage [43]. Therefore, we targeted patients who are in the contemplation, preparation, or action stages of achieving the target goal of 10,000 steps a day.

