V4	Hospital visit 2	End of week 8	Check app use and equipment Check for adverse events Intervention: coach goals and coping strategies Collect medication and combination therapy status
V5	Interim hospital visit	End of week 12	Collect physical data: blood tests to measure HbA_1c_, FBG, LDL cholesterol, HDL cholesterol, TG, and eGFR; urinalysis; and body weight and BP measurements Check app use and equipment Check for adverse events Intervention: coach goals and coping strategies Collect medication and combination therapy status Conduct surveys (Textbox 4)
V6	Hospital visit 4	End of week 16	Check app use and equipment Check for adverse events Intervention: coach goals and coping strategies Collect medication and combination therapy status
V7	Hospital visit 5	End of week 20	Check app use and equipment Check for adverse events Intervention: coach goals and coping strategies Collect medication and combination therapy status
V8	End of the intervention	End of week 24	Collect physical data: blood tests to measure HbA_1c_, FBG, LDL cholesterol, HDL cholesterol, TG, and eGFR; urinalysis; and body weight and BP measurements Collect medication and combination therapy status Check for adverse events Conduct surveys (Textbox 4) Assess usefulness and usability
V9	End of follow-up	End of week 36	Collect physical data: blood tests to measure HbA_1c_, FBG, LDL cholesterol, HDL cholesterol, TG, and eGFR; urinalysis; and body weight and BP measurements Collect medication and combination therapy status Check for adverse events Conduct surveys (Textbox 4)

^a^HbA_1c_: hemoglobin A_1c_.

^b^FBG: fasting blood glucose.

^c^LDL: low-density lipoprotein.

^d^HDL: high-density lipoprotein.

^e^TG: triglyceride.

^f^eGFR: estimated glomerular filtration rate.

^g^BP: blood pressure.

Surveys—9 surveys assessing type 2 diabetes–related behaviors and outcomes.

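### The adverse-event severity comparison has no level for patients without an event, so it compares grades only among events that occurred and can favour the arm with extra mild events

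*Protocol article*

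**What the plan says.** The safety paragraph of Statistical Analysis (protocol article) contains three comparisons.

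- Named safety events: "We will compare the proportion of incidences of hypoglycemia, joint pain, significantly elevated BP" and worsening of joint pain, by Fisher exact test.
- Other adverse events, coded by Preferred Term and System Organ Class: "their incidence proportions will be compared between groups using Fisher exact test".
- Severity: "The severity of each incidence will be categorized into 3 grades (low, moderate, and high), and their between-group comparison will be conducted", using the CMH test.

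The severity sentence names the unit that is graded (the incidence), three grades and the test. It gives no grade for a patient without an event, no rule for several events in one patient, and no scores or strata.

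The same section defines the safety population by patient: "SAS is the set of all patients who used the StepAdd app or the placebo app at least once after randomization". It assigns all safety analyses to that set. Table 2 under Intervention Process schedules adverse-event checks at every visit from V2 to V9, for example "Check app use and equipment Check for adverse events Intervention: coach goals and coping strategies" at V3 to V7. One patient can therefore contribute more than one event.

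**The concern.** Two mechanisms follow from grading each incidence on a three-level scale.

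**Conditioning on occurrence.** With only low, moderate and high available, a patient without an event has no value to contribute. The comparison is then made among events, or affected patients, that came into being after randomisation. An arm with the same moderate and high events plus additional mild ones has a lower mean grade, and the test can declare it better. This does not depend on repeated events. It happens even if each affected patient is counted once.

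**Repeated events.** If every event is a row, several rows can come from one patient. The CMH test treats rows as independent. If a patient's events tend to have similar severity, the null variance is too small and the test rejects too often.

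The pattern is plausible here. The intervention aims to increase walking, and Secondary Outcomes lists lower-back and leg pain and subjective hypoglycemia as safety outcomes. Extra mild events are one natural form that harm could take. Safety is also part of the stated objective in the Abstract.

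**Working it through.** **Number per arm.** The plan gives no figure for the severity comparison, so the sample-size statement serves only to set the number of patients. Patient Recruitment states: "To detect 0.35% difference in the primary outcome (change in HbA_1c_ level), assuming an SD of 0.74% as seen in a previous study", and "to achieve a 2-sided significance level of .05 and a statistical power of 80%, the minimum sample size is 72 patients per group".
- Normal approximation: n = 2(1.960 + 0.842)² × 0.74² / 0.35² = 2 × 7.849 × 0.5476 / 0.1225 = 70.2, so 71.
- The t-based solution is 71.15, so 72. This reproduces the stated figure.
- With 10% dropout: 72 / 0.9 = 80 per arm, 160 in total, as stated.

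**Illustration of conditioning (assumed counts).** Arm A has 40 low, 8 moderate and 2 high. Arm B has 10, 8 and 2. Each event is in a different patient. The test is the unstratified CMH row-mean-score statistic Q = (N − 1)r² on 1 degree of freedom, where r² = (n_A n_B / N²)(difference in means)² / (pooled variance with divisor N).

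*Three grades, scores 1 to 3, events only (N = 70):*
- Mean A = (40 + 16 + 6)/50 = 1.24. Mean B = (10 + 16 + 6)/20 = 1.60.
- Pooled mean = 94/70 = 1.343. Pooled variance = 150/70 − 1.343² = 0.3396.
- r² = (50 × 20 / 4900) × 0.36² / 0.3396 = 0.0779.
- Q = 69 × 0.0779 = 5.37, p = 0.020, in favour of A.

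*Four levels, none = 0, all patients (N = 160):*
- Mean A = 62/80 = 0.775. Mean B = 32/80 = 0.40.
- Pooled mean = 94/160 = 0.5875. Pooled variance = 150/160 − 0.5875² = 0.5923.
- r² = (80 × 80 / 25,600) × 0.375² / 0.5923 = 0.0594.
- Q = 159 × 0.0594 = 9.44, p = 0.002, against A.

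The moderate and high counts are identical in the two arms, yet the sign of the conclusion reverses.

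**Occurrence in the same illustration.** Fisher exact test on 50/80 against 20/80 gives p < 0.001 against A.

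**Type I error if every event is a row.** Simulation with no true difference, 80 per arm, 4000 trials per setting, grades split 60/30/10% from a latent normal variable with a patient effect, and the same CMH statistic at nominal 5%. Event rates, overdispersion, correlation and grade split are all assumptions, because the article gives no adverse-event rates. Overdispersed counts are negative binomial with dispersion 1. Results from two runs agree to within about one percentage point where they overlap.

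| Mean events per patient | Counts | Correlation 0 | 0.3 | 0.5 |
|---|---|---|---|---|
| 0.3 | overdispersed | 5.0% | 6.3% | 7.6% |
| 0.5 | overdispersed | 4.4% | 7.3% | 10.6% |
| 1 | Poisson | 5.7% | 7.6% | not run |
| 1 | overdispersed | 4.7–5.5% | about 10% | about 14% |
| 2 | overdispersed | 5.0% | about 15% | 20–21% |
| 3 | overdispersed | 4.5% | about 20% | about 28% |

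With one row per patient (worst grade, none = 0), rejection was between 4.3% and 5.4% in every setting.

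**The case against.** **The sentence may only describe how events are graded.** Adverse events are always graded one by one at collection, and the sentence does not say what a row in the test is. The neighbouring sentences speak of proportions of incidences, which make sense only as proportions of patients, so the word may be used loosely. The article is condensed, and a counting rule for repeated events often sits in an analysis plan that is not shown. This stands against the repeated-events part. A reader might infer that the plan enters repeats as independent observations and that its severity p value is therefore wrong. The text suggests that reading but does not state it, and without within-patient correlation rejection stays near 5%. Nor can frequent hypoglycemia be presumed: the inclusion criteria require no hypoglycemic symptoms in the 12 weeks before V0.

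**All safety analyses use the full safety set, so patients without events may be included.** This stands only in part. Naming the set does not give such patients a value on a scale of low, moderate and high. A worst-grade rule per affected patient would still leave the comparison conditional on having an event unless a fourth level were added, and the sentence fixes three.

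**Occurrence is tested separately.** This limits the consequence. A reader might infer that the trial could declare the more harmful arm safer overall. The documents do not support that: in the illustration the Fisher test shows the excess clearly. It would be missed mainly if extra mild events fell in patients already affected or were spread thinly over many coded terms.

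**Severity among events, shown beside incidence, is a recognised pairing.** That is fair for a descriptive table. It does not justify a between-group test of the conditional quantity as a randomised comparison.

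**Conclusion.** The point holds for the severity comparison as written. Three grades without a level for no event make the test conditional on occurrence after randomisation, and a modest excess of mild events is enough to reverse its direction (p = 0.020 for, against p = 0.002 against, on assumed counts).

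The type I error concern is conditional. It needs repeated events to enter as separate rows and severity to correlate within patients. At 0.3 to 0.5 events per patient, rejection is mostly about 7% to 8%, with 6.3% and 10.6% at the corners tried. It reaches 10% to 28% only at assumed overdispersed means of 1 to 3 events with correlation 0.3 to 0.5.

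The effect is confined to one safety comparison with no decision rule attached. The occurrence tests, the primary outcome and the sample size are untouched. The sentence should be changed, but the safety assessment as a whole is not undermined.

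**What to change.** Replace the severity sentence with text along these lines: each patient in the safety analysis set is classified once by the worst grade experienced (none, low, moderate, high), for each event type and overall. Groups are compared with the CMH row-mean-score test using stated scores. Numbers of events, and severity among events, are reported descriptively without a test.

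The cost is one sentence. No new data are needed and the test family is the same. The one drawback is that, with a level for none included, the severity test partly overlaps with the Fisher comparison of occurrence. The descriptive table of severity among events keeps the separate information visible.

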## Results

Recruitment began on January 1, 2023. As of September 5, 2023, we have recruited 44 patients. We expect the trial to be completed by October 8, 2025, with the follow-up observation period being completed by December 31, 2025. We anticipate completing the analysis by March 30, 2026.

